#### Primary outcomes

##### Exacerbations of IPF

The frequencies of acute exacerbations of IPF, which is assessed by AEIPF-related hospitalization, is the primary outcome measure. AEIPF is characterized by significant respiratory deterioration, with an unknown cause within the past 1 month [28]. If the interval between any two AEIPF-related hospitalizations is less than 7 days, they are considered as one AE. The AE will be recorded at every visit, and the total number in the whole process (1-year treatment period) will be calculated. A higher number in a given period indicate the deterioration of IPF and a worse prognosis. A lower number in the experimental group will indicate better efficacy.

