## Introduction

Idiopathic pulmonary fibrosis (IPF) is a progressive interstitial lung disease with poor prognosis and short median survival [1]. The etiology remains not completely clear [2]. With a low prevalence rate, some scholars consider it as a rare disease [3]. In China, it has also been included in the list of rare diseases in 2018. However, different studies show that it has been more common in recent years [4, 5]. After diagnosis, IPF patients will follow a median survival of 2–5 years [5]. Data also shows that IPF patients in Sweden will spend an annual average of $13,975 for hospitalization [6]. In America, a total of 2 billion dollars has been spent on the prevention and treatment of IPF every year [7]. IPF has caused a heavy socio-economic burden.

Although different studies have been performed in recent years, the available treatments remain limited. As reported in the latest international guidelines for IPF, only pirfenidone and nintedanib are recommended in clinical application [8]. They could improve pulmonary function, quality of life, and exercise capacity and delay the disease progression for IPF patients [9–11]. However, the related side effects have also been reported. One study showed that a total of more than 10% of IPF patients taking pirfenidone or nintedanib have discontinued medication permanently due to side effects [12], and their long-term effects are still under debate. Up to now, evidences for other drugs are still insufficient [13–20]. Limited researches have also been performed on non-drug treatment for IPF [21]. However, the levels of the available evidences are also low. It is urgent to conduct further researches on the treatments of IPF [22].

Traditional Chinese medicine (TCM) has different treatments and certain efficacy for respiratory diseases. Chinese herbal medicine (CHM) is the most used measures. According to TCM theory and our previous studies, IPF should be treated according to *feiwei* or *feibi*, and the core TCM pathogenesis includes vital *qi* deficiency, lung collaterals obstruction, phlegm and blood stasis, and accumulation of damage. We have also developed a TCM therapeutic scheme for IPF based on the above studies. Then, the CHM formulation has been optimized to Jin-shui Huan-xian granule (JHG) by clinical application and basic experiments.

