##### All-cause mortality

Any death for IPF patients in this study with any cause will be recorded and counted. All-cause mortality will be calculated at the end of the treatment in each group. A lower number in the experimental group indicate a better efficacy for the intervention in improving prognosis.

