##### Data management and statistical analysis plan

Statistical analysis will be conducted both in the intent-to-treat (ITT) and pre-protocol (PP) data. ITT analysis will be applied to analyze the safety data. All the data from any included patients will be analyzed regardless of their withdrawal from the trial. The PP analysis will be adopted to assess the efficacy of the interventions. If data permit, sub-group analysis will also be performed to help clarify the therapeutic effect of interventions.

All the *P* values will be set as two-tailed with a significant level of 0.05. Measurement data will be shown with mean ± SD, median, and inter-quartile range. Count data will be presented by frequency or composition ratio. Analysis of variance (ANOVA) will be used to test for the differences in continuous variables, with the chi-square test for categorical variables. If necessary, the paired *t*-test will be applied to intra-group comparison data with normal distribution and homogeneous variance, and the Wilcoxon signed-rank sum test will be used for non-normal distribution or uneven variance. Repeated-measures ANOVA will be used to test the continuous response variables that are measured at more than two time points for the same patient, such as 6MWT, clinical symptoms and signs, mMRC, and HRQoL. To improve the quality of data, all the data management and statistical analysis will be conducted by the Jiangsu Famous Medical Technology Co., Ltd. in Nanjing, China.

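### The primary exacerbation outcome is a raw one-year total read as lower-is-better, with no allowance for time at risk or death, so unequal early loss biases it

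*Protocol article*

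**What the plan says.** Under Exacerbations of IPF, the article makes the frequency of acute exacerbations, assessed by hospitalisation, a primary outcome. Events are recorded at each visit and "the total number in the whole process (1-year treatment period) will be calculated". The direction of benefit carries no condition on survival or time observed: "A lower number in the experimental group will indicate better efficacy".

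Under Data management and statistical analysis plan, the between-group tests are given in one sentence: "Analysis of variance (ANOVA) will be used to test for the differences in continuous variables, with the chi-square test for categorical variables". Repeated-measures ANOVA is reserved for continuous measures taken at several visits. For display, "Count data will be presented by frequency or composition ratio". No rate, person-time or time-to-event method appears.

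On analysis sets, the same section keeps withdrawn patients in the ITT data ("All the data from any included patients will be analyzed regardless of their withdrawal from the trial") but says of efficacy: "The PP analysis will be adopted to assess the efficacy of the interventions".

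Death appears in two other places. It is one of the events that end progression-free status, which is another primary outcome, and it is a secondary outcome of its own: "All-cause mortality will be calculated at the end of the treatment in each group". Neither is linked to the exacerbation count.

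**The concern.** A total is comparable between arms only if both arms are observed for the same time. The article's own explanation of the outcome refers to a number within a given period, yet nothing makes that period equal across patients. Someone who dies or leaves in month 2 without a hospitalised event contributes 0, the same as someone followed event-free for a year.

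Early loss is likely to be substantial in this disease. The Introduction says that "IPF patients will follow a median survival of 2–5 years" after diagnosis, and the Eliminated criteria and Sample size sections allow for up to 20% withdrawal or drop-out. If loss is greater in one arm, that arm's count falls for a reason unrelated to exacerbation risk, and the stated rule reads the fall as efficacy. If loss is greater in the control arm, the bias runs against the granule.

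**Working it through.** **No figure in the plan to reproduce.** The article gives no exacerbation rate, no dispersion and no expected follow-up time. The Sample size section is based on 6MWD. Rates and loss splits below are therefore assumptions, shown as ranges.

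**Inputs from the article.** 156 patients per group; two-sided 0.05; one-year treatment period; up to 20% withdrawal; median survival 2–5 years.

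**How much loss is plausible.** If survival is exponential (assumption), one-year mortality is 1 − 0.5^(1/5) = 0.129 at a 5-year median and 1 − 0.5^(1/2) = 0.293 at a 2-year median. Mean follow-up within the year is (1 − e^−λ)/λ = 0.934 and 0.845 years.

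**Size of the spurious effect, loss unrelated to risk.** With the same true rate in both arms, the expected raw-count ratio is the ratio of mean follow-up. If a fraction p is lost at uniformly distributed times, mean follow-up is 1 − p/2.

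- 25% vs 15%: (1 − 0.125)/(1 − 0.075) = 0.875/0.925 = 0.946, a spurious reduction of 5.4%.
- 30% vs 10%: (1 − 0.15)/(1 − 0.05) = 0.85/0.95 = 0.895, a spurious reduction of 10.5%.
- Equal loss: ratio 1.00, no bias.

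If losses centre on week 13, each costs 0.75 year. Then 30% vs 10% gives 0.775/0.925 = 0.838.

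**Type I error.** Simulated trials with 156 per arm, equal true rates, uniform loss times and a two-group comparison of raw counts, at 0.3, 0.6 and 1.0 events per year:

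| Loss | Poisson counts | Overdispersed counts (gamma frailty, shape 1) |
|---|---|---|
| 20% vs 20% | 5.0–5.1% | about 5% |
| 25% vs 15% | 5.9%, 6.4%, 7.7% | 5.3–6.0% |
| 30% vs 10% | 7.8%, 11.2%, 14.9% | 7.8%, 8.6%, 10.0% |

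**If sicker patients are lost more often.** A separate simulation let the same frailty drive both exacerbation and loss, with a true ratio of 1.00:

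| Loss | Raw-count ratio | Rate ratio adjusted for follow-up |
|---|---|---|
| 20% vs 10% | 0.88–0.90 | 0.94–0.95 |
| 30% vs 10% | 0.77–0.78 | 0.88 |
| 40% vs 20% | 0.75 | 0.87–0.88 |

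Adjusting for follow-up restores a ratio of about 1.00 when loss is unrelated to risk. When loss is related to risk, it removes only part of the bias.

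**The case against.** The strongest reply has four parts.

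1. **The test is not named.** A reader might infer that the count will be compared by ANOVA or chi-square. The article assigns those tests to continuous and categorical variables and says nothing specific about exacerbations, and a fuller analysis plan may exist. This stands. What remains is that the endpoint summary and the direction-of-benefit rule are published as a raw total, and any test of an unadjusted total has the same defect.

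2. **Efficacy is assessed per protocol.** A reader might infer that every early drop-out enters the efficacy analysis as a zero. The Eliminated criteria withdraw patients with low adherence or who stop the drug themselves, so many would probably leave that set. This stands: the drop-out part of the point applies to the ITT data. The per-protocol set replaces truncated counts with selection after randomisation, and the article does not say whether patients who die leave it.

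3. **Death is counted elsewhere.** A reader might infer that a treatment causing excess early death would be judged effective by the trial. The documents do not support that, because the same deaths count against it in the progression-free primary outcome and are reported as all-cause mortality. The exacerbation endpoint taken alone would still credit them.

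4. **The loss splits are assumed.** This also stands. The effect is modest at 25% vs 15%, smaller with overdispersed counts, and absent with equal loss. The 13–29% mortality range applies survival after diagnosis to a trial of stable patients, and the article does not say whether deaths are already inside the 20% allowance, so the two should not simply be added.

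**Conclusion.** The point holds in limited form. As published, a primary outcome is an unadjusted total with an unconditional lower-is-better reading, and the article provides no method that uses time at risk or deals with death. In the ITT data, and for any deaths kept in the per-protocol set, unequal early loss biases this endpoint in favour of the arm with more loss.

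For assumed losses between 25% vs 15% and 30% vs 10%, equal true rates and loss unrelated to risk, the spurious reduction is 5.4–10.5%. Two-sided type I error is 5.9–14.9% with Poisson counts and 5.3–10.0% with overdispersed counts. The bias is larger if loss is early or concentrated in sicker patients, and nil if loss is equal. These sizes depend on assumed rates of 0.3–1.0 per year and on loss differences that the article neither gives nor predicts. They show the endpoint's sensitivity and do not forecast the trial's result.

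**What to change.** - **Main analysis of this outcome.** In all randomised patients, fit a negative binomial regression of the exacerbation count on arm, with the log of time from randomisation to death, loss or week 52 as offset. Report a rate ratio with its 95% CI.
- **Paired analysis.** Because loss may be related to exacerbation risk, and the offset then corrects only part of the bias, prespecify time to first exacerbation hospitalisation or death (log-rank test and Cox model) alongside it.
- **Interpretation.** Amend the direction-of-benefit sentence so that a lower count is read only per unit of follow-up and together with mortality in each arm.

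**Cost.** Admission, death and last-contact dates must be available for every randomised patient. The analysis text must be amended, including the statement that efficacy rests on the per-protocol set as far as this outcome is concerned. No extra visits are needed. The hospitalisation-based event definition need not change. Adding exacerbation deaths outside hospital as events would alter the primary outcome after enrolment has begun (70 patients at submission) and is not required, because the paired analysis already counts every death.

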##### 6MWD

6MWD is adopted to assess the exercise capacity of IPF patients. It is evaluated by the distance an IPF patient can walk as fast as he/she can in 6 min. A longer distance indicates better exercise capacity for IPF patients.

##### Proportion of disease progression-free survivals

The endpoints of free disease progression in this study include any of the following events [29]: forced vital capacity (FVC) decreased by 10%, diffusing capacity percentage of the predicted value (DLCO%) by 15% compared to baseline, patient death, and lung transplantation. At the end of treatment, the proportion of the patients without any of the above endpoints will be calculated.

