### Outcome measures

Assessment will be performed by outcome measures at baseline, end of treatment, and given follow-up points. The primary outcomes include frequencies of AEIPF, 6-min walking distance (6MWD), and the proportion of patients with disease progression-free. The secondary outcomes include pulmonary function, all-cause mortality, clinical symptom and signs, dyspnea, and health-related quality of life (HRQoL).

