#### Secondary outcomes

##### Pulmonary function

FVC and DLCO% will be examined at baseline and at the end of the treatment. A positive change will indicate the improvement of pulmonary function.

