#### Safety outcomes

We will also evaluate the safety of interventions in this study. Safety outcome measures, including routine blood, urine, and stool tests; liver and kidney function tests; and electrocardiography, will be examined. Any adverse events will also be recorded and managed according to the degrees of damage at any time they occur during the treatment period. Then, we will also report to the ethics committee for further management. Based on our previous studies, the possible adverse events are transient gastrointestinal discomfort without the need for intervention.

Pulmonary function, routine blood, urine and stool tests, liver and kidney function tests, and electrocardiography will be tested and recorded at baseline (week 0), at 6 months after treatment (week 26), and at the end of the treatment (week 52). 6MWT, clinical symptoms and signs, MMRC, CAT, SF-36, SGRQ, and ATAQ-IPF will be completed and recorded at week 0, week 13, week 26, week 39, and week 52 in the process of trial.

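### The primary progression-free outcome is a raw end-of-treatment proportion judged in the per-protocol set, in effect a completer analysis; the lung-function visit times also need reconciling

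*Protocol article*

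**What the plan says.** All references are to the Protocol article.

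- **Outcome measures** gives the endpoint primary status: "The primary outcomes include frequencies of AEIPF, 6-min walking distance (6MWD), and the proportion of patients with disease progression-free".
- **Proportion of disease progression-free survivals** lists the events as "forced vital capacity (FVC) decreased by 10%, diffusing capacity percentage of the predicted value (DLCO%) by 15% compared to baseline, patient death, and lung transplantation", and then fixes the summary: "At the end of treatment, the proportion of the patients without any of the above endpoints will be calculated".
- **Data management and statistical analysis plan** gives the method for such an outcome, "with the chi-square test for categorical variables", and the analysis set: "The PP analysis will be adopted to assess the efficacy of the interventions". The section opens by naming both intention-to-treat and per-protocol data, but then assigns intention-to-treat to safety. It names no time-to-event method.
- **Drop-out criteria** and **Eliminated criteria** take in patients who are lost to visits, stop the study drug themselves, use a prohibited drug, or take less than 80% or more than 120% of their medication. Eliminated criteria puts withdrawal at no more than 20%, and **Sample size** allows 20% for drop-out.
- Lung-function times appear twice. **Pulmonary function** says "FVC and DLCO% will be examined at baseline and at the end of the treatment". **Safety outcomes** says that pulmonary function "will be tested and recorded at baseline (week 0), at 6 months after treatment (week 26), and at the end of the treatment (week 52").

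**The concern.** Decline, transplantation and death accrue over 52 weeks, in a disease where patients who deteriorate may well be the ones who stop coming. A proportion taken at the end of treatment in the per-protocol set uses, in practice, those who stayed and adhered. If the patients who leave have progressed more often than those who stay, each arm's progression-free proportion is too high, and the arm that loses more of them is flattered. A difference between arms can then arise with no treatment effect, on a primary outcome.

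The two lists of lung-function times matter for the same reason. A week-26 measurement is what allows a decline to be recorded in a patient who leaves between weeks 26 and 52. If only baseline and end-of-treatment values were used, that decline would not be seen. It is also left open whether a decline present at week 26 but recovered by week 52 is an event.

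**Working it through.** The protocol states no progression-free rate and no loss rate by arm, so there is no figure for this endpoint to reproduce. The one related figure is the drop-out allowance: 124 / 0.80 = 155 per group, against 156 stated, which is consistent with planning for about 20% loss.

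**Inputs.** From the protocol: 156 per arm, and loss of up to 20%. Assumed: a true progression-free proportion of 60% in both arms, and the loss rates by arm shown below.

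**1. Lost patients dropped (the per-protocol route).** Let *P* be the true progression-free proportion, *L* the share lost and *q* the progression-free proportion among the lost. The proportion among those who remain is (*P* − *qL*) / (1 − *L*).

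| Assumption on the lost | Loss | Observed proportions | Spurious difference |
|---|---|---|---|
| Unrelated to progression (*q* = 0.60) | 20% vs 10% | 0.48/0.80 = 60.0% vs 0.54/0.90 = 60.0% | 0 |
| Half as often progression-free (*q* = 0.30) | 20% vs 10% | 0.54/0.80 = 67.5% vs 0.57/0.90 = 63.3% | 4.2 points |
| All progressors (*q* = 0) | 20% vs 10% | 0.60/0.80 = 75.0% vs 0.60/0.90 = 66.7% | 8.3 points |
| All progressors (*q* = 0) | 20% vs 15% | 75.0% vs 0.60/0.85 = 70.6% | 4.4 points |
| All progressors (*q* = 0) | 20% vs 20% | 75.0% vs 75.0% | 0 (both arms too high) |

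**2. Lost patients kept and counted as event-free (a possible literal reading, not a stated rule).** With loss unrelated to progression and no event recorded among the lost, the apparent proportion is 1 − (1 − *P*)(1 − *L*). Losses of 25% versus 15% give 1 − 0.40 × 0.75 = 70% versus 1 − 0.40 × 0.85 = 66%, a spurious 4 points.

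**3. How much the handling of the lost matters within one arm.** Take 156 patients, 31 lost (20%) and 75 of the 125 observed progression-free (60%, assumed):

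- dropped: 75/125 = 60.0%
- counted as progression-free: (75 + 31)/156 = 67.9%
- counted as progressed: 75/156 = 48.1%

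The range from 48.1% to 67.9% is 31/156, about 20 points: simply the share lost.

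**4. What time-to-event analysis does and does not repair.** In the all-progressors case, suppose that the lost patients had met a lung-function threshold at week 26 and left afterwards. Each is then an event in an all-randomised analysis, and both arms return to 60%. Suppose instead that they left before week 26 with nothing recorded. They are then censored at baseline, contribute nothing, and the Kaplan-Meier week-52 figures are again 75.0% and 66.7%. Counting them as progressed gives 60% in both arms, which is why the sensitivity analysis is needed.

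**5. The two visit lists.** Pulmonary function gives two times; Safety outcomes gives three. The first list does not say that no other test is done, and the second is the explicit schedule.

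**The case against.** The strongest case against is that every patient has the same planned 52 weeks, so a week-52 proportion is a legitimate summary. How to classify a patient with no week-52 assessment is ordinary analysis-plan content that a condensed article may omit. Lung-function progression can be dated only to a visit, so time-to-event adds limited precision for those components. Censoring also assumes uninformative loss.

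Much of this stands. The absence of a missing-data rule is not the point here. The point is what the article does fix: a raw proportion, a chi-square test and a per-protocol set for efficacy, which together remove patients after randomisation.

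Three stronger readings are tempting and are not supported:

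- A reader might infer that patients lost without an event will be counted as progression-free. No section says so; the per-protocol wording points to their leaving the denominator.
- A reader might infer that the arm with more early loss always looks better. In the per-protocol set this needs loss related to progression; otherwise the bias is zero, as the first row of the table shows.
- A reader might infer that 20% of patients will be missing, or that week-26 lung function will not exist. The 20% in Eliminated criteria is a ceiling, it covers non-adherent patients whose outcomes may be known, and their records are kept. The Pulmonary function section does not exclude a week-26 test.

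**Conclusion.** The point holds as a weakness in the chosen analysis of a primary outcome, and it should be changed. As fixed, the progression-free comparison is in effect a completer analysis. It is open to bias where loss is related to progression and differs by arm. In the per-protocol illustrations the spurious difference runs from nil to 8.3 points; the upper end requires that all losses are progressors and that losses are 20% versus 10%. These rates are assumptions, and the documents do not indicate which arm would lose more.

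The difference between the two lung-function lists is real and must be reconciled, because it decides whether a decline before loss can enter the endpoint. It does not show that week-26 data are absent.

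**What to change.** - Analyse all randomised patients by time from randomisation to the first of: the FVC or DLCO% threshold (at week 26 or 52), death or transplantation.
- Censor event-free patients at their last lung-function assessment, but count any death or transplantation that is recorded, even if it comes after that assessment.
- Compare arms by log-rank test with a Cox hazard ratio, and report the Kaplan-Meier week-52 proportion in place of the raw one.
- Add a sensitivity analysis that counts patients lost without an event as progressed. The per-protocol result can stay as supportive.
- Analyse all-cause mortality in all randomised patients, censored at the date last known alive.
- Reconcile the Pulmonary function section (baseline and end) with Safety outcomes (weeks 0, 26 and 52), and state that a week-26 decline counts as an event.

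The cost is protocol and analysis-plan wording: the week-26 test is already in the schedule, and the article reports 70 of 312 patients enrolled at submission. There are two small downsides. Dates of lung-function progression are known only to the visit, and censoring still assumes uninformative loss and gains no lung-function information from event-free patients lost before week 26.
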